## 3. Statistical Methods

The presentation of continuous variables will adhere to the prescribed statistical methodology, as delineated in the relevant sections of this study. The reported variables will comprise either the mean and standard deviation or the median and interquartile range, as required. With regard to dichotomous and nominal variables, the resulting data will be presented in the form of a tally and the corresponding percentage. A range of statistical tests will be employed in the univariate analysis, including the Mann–Whitney U-test, Student’s *t*-test, Kruskal–Wallis test, Wilcoxon test, Fisher exact test, Chi-square test, and Kaplan–Meier test. In the event of incomplete datasets, no attempts will be made to supplement the information in question.

Multivariable analyses will be conducted employing the logistic regression model and the Cox proportional hazards model. The variables to be included in the logistic regression analysis will be selected using the Lasso-based variable selection method. Any noteworthy inconsistencies between the study groups will be addressed through the application of propensity score weighting. To estimate the causal effect of exposure on outcomes, a doubly robust approach will be employed comprising combination regression with inverse probability treatment weighting (IPTW) by propensity score. Multivariable analyses will be conducted by employing the logistic regression model and the Cox proportional hazards model. The variables to be included in the logistic regression analysis will be selected using the Lasso-based variable selection method. Any noteworthy inconsistencies between the study groups will be addressed through the application of propensity score weighting. To estimate the causal effect of exposure on outcomes, a doubly robust approach will be employed comprising combination regression with inverse probability treatment weighting (IPTW) by propensity score. In order to accomplish this, a propensity score that balances for covariates will be developed with the objective of minimizing discrepancies between the groups in question.

A total sample population of 630 patients was calculated as sufficient to detect a significant difference in the rate of reverse left ventricular remodeling, with 384 patients undergoing surgical mitral valve repair and 246 patients undergoing transcatheter mitral valve repair. This study was powered at 80% with a two-tailed alpha level of 0.05. In order for a *p*-value to be deemed statistically significant, it must be less than 0.05. All statistical analyses were performed with the aid of the R software package developed by the R Foundation for Statistical Computing in Vienna, Austria.

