#### 2.2.1. Primary

The primary endpoint of this study is the degree of LV remodeling as assessed by the Left Ventricular End-Diastolic Volume Index (LVEDVI) at the 10-year follow-up.

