The primary objective of the trial is to evaluate the efficacy of the intervention in terms of left ventricular remodeling. This will be accomplished by quantifying the change in the Left Ventricular End-Diastolic Volume Index (LVESVI) at the time of hospitalization and at regular intervals following the procedural intervention, employing transthoracic echocardiography (TTE).

Secondary endpoints.

The main secondary endpoint is mortality, which will be evaluated based on the total number of deaths from any cause.

In addition to the primary endpoints, the trial has defined the following secondary endpoints:Perioperative management.

The variables to be evaluated are as follows: operative time, cardiopulmonary bypass time, cross-clamp time, blood loss, and transfusions.

○Cardiopulmonary bypass parameters.

Information pertaining to the elapsed time of myocardial ischemia, the duration of cardiopulmonary bypass, and the method of cardiac cardioplegia perfusion (retrograde or antegrade) will be extracted from the dataset.

○Blood loss and transfusions. Supplementary Table S1 [35,36,37]○Reoperation for bleeding. Supplementary Table S1 [35,36,37]

A reoperation to reopen the chest for the management of excessive bleeding is indicated in cases where bleeding persists. A reoperation for bleeding is defined as any subsequent surgical procedure necessitated by the necessity to address excessive bleeding in a patient in whom the sternum was left open during the initial operation. It is essential to recognize that reopening the chest for hemodynamic instability without severe bleeding and for the purpose of puncturing the pericardium or pleura or inserting a chest tube for retained blood syndrome is not regarded as a reoperation for bleeding.

▪Functional Status.•MACE (major adverse cardiac event).

A MACE is specified as an unweighted composite score. It consists of the following components:○Death.○Stroke.○Mitral valve re-intervention.○Worsening heart failure (+1 NYHA Class).○CHF hospitalization.•Reoperation.

All subsequent surgical procedures, including reoperations for MR, will be meticulously documented, and the incidence of reoperation will be evaluated through a rigorous time-to-event analysis.

Peak VO2.

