The objective of this study is to evaluate improvements in quality of life (QOL) from baseline utilizing a comprehensive array of disease-specific instruments. These include the Minnesota Living with Heart Failure (MLHF) score, the disease-specific Duke Activity Status Index (DASI), the Short Form-12 general health status index, and the EuroQol 5-D measures of health state preference, with an emphasis on both individual and societal perspectives.

The Minnesota Living with Heart Failure Questionnaire is a quantitative assessment tool designed to evaluate the impact of heart failure and its management on patients across a range of domains, including physical, psychological, and social functioning. The DASI is a multidimensional questionnaire that assesses the cardiovascular impact of four domains of adult activity, each associated with distinct levels of oxygen uptake: ambulation, personal care, domestic tasks, sexual function, and the pursuit of leisure activities. The SF-12 represents a comprehensive quality-of-life assessment tool encompassing eight distinct dimensions: physical activity, social activity, role/physical, body pain, general mental health, role/emotional, vitality, and general health perception. The SF-12 and the EuroQoL 5-D are both instruments designed to assess health-related quality of life. The EuroQol 5-D is a psychometric instrument that yields a succinct descriptive profile comprising five distinct dimensions. The instrument evaluates five domains: (i) anxiety/depression, (ii) pain/discomfort, (iii) usual activities, (iv) self-care, and (v) mobility. Furthermore, it incorporates an evaluation of the individual’s perception of their own health status.

▪Safety.
•Reoperation.•All reoperations, particularly those for mitral regurgitation, will be recorded. Freedom from reoperation will be evaluated.•Adverse events.

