## 4. Ethics and Dissemination

### 4.1. Implications for Treating Patients Undergoing Transcatheter Versus Standard Surgical Mitral Valve Operation for Secondary Mitral Regurgitation

A thorough examination of the data from this registry will yield current insights for a substantial number of SMR patients with a comprehensive follow-up period. The multicenter nature of this registry is expected to reduce the risk of bias related to institutional volume and surgical experience. It is anticipated that all participating centers will perform a minimum of 25 procedures per annum for SMR. Furthermore, a plan for mitral surgery must be devised and implemented, allowing for effective follow-up and management of late occurrences following replacement surgery or primary repair of SMR. It is anticipated that the data collected will yield insightful information regarding the influence of distinct surgical approaches on conventional mitral valve surgery and TEER. This will facilitate the evaluation of LV remodeling in long-term follow-up. Furthermore, this research will offer conclusive data on the effectiveness of various standard mitral valve surgical techniques in a setting where mortality rates are elevated, with a 50% mortality rate, as well as long-term mortality rates for patients who have undergone TEER.

A comparison of the results obtained from the analysis of S-SMVp, which involved three distinct procedures, and TMVp for use in SMR procedures, was conducted. The following comparative analysis is based on data from a multicenter dataset, which allows for a comprehensive overview of the findings. The objective is to identify the most effective intervention for left ventricular remodeling and enhanced left ventricular ejection fraction within a 10-year timeframe. It would be beneficial to ascertain whether there is a difference in the incidence of death from all causes at 10 years following S-SMVp or TMVp. It would also be advantageous to determine whether patients with increased LVEF also have more favorable HF symptoms. A related question is which of the two procedures (S-SMVp and TMVp) achieves an immediate reduction in MR to moderate or lower levels and what proportion of individuals can derive benefit from this result.

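### With deaths expected before 10 years and a rule of not supplementing incomplete data, the primary LVEDVI analysis becomes a comparison of imaged survivors, which weighting on baseline covariates cannot correct

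*Protocol article*

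**What the plan says.** Section 2.2.1 defines the primary endpoint as "the degree of LV remodeling as assessed by the Left Ventricular End-Diastolic Volume Index (LVEDVI) at the 10-year follow-up". Section 2.3 adds that the volume index is measured by transthoracic echocardiography at hospitalization and at regular intervals afterwards.

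Section 3 (Statistical Methods) gives one rule for missing data: "In the event of incomplete datasets, no attempts will be made to supplement the information in question". Its list of univariate tests ends with "Fisher exact test, Chi-square test, and Kaplan–Meier test". For adjusted work it says "Multivariable analyses will be conducted employing the logistic regression model and the Cox proportional hazards model", combined with propensity-score weighting in a doubly robust approach. It names no longitudinal model and no method that accounts for death.

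Section 4.1 places the study "in a setting where mortality rates are elevated, with a 50% mortality rate" and asks "whether there is a difference in the incidence of death from all causes at 10 years following S-SMVp or TMVp". That is the same horizon as the primary endpoint.

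For reoperation, section 2.3 says "the incidence of reoperation will be evaluated through a rigorous time-to-event analysis" and, under safety, "Freedom from reoperation will be evaluated". Death is not mentioned as a competing event.

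**The concern.** A 10-year LVEDVI exists only for a patient who is alive and imaged at 10 years. Under the stated rule everyone else leaves the primary comparison.

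Two statements in the article suggest that this loss is informative. Section 4.2 calls left ventricular remodeling an adverse prognostic sign in ischemic heart disease, so the outcome is related to who dies. The hypothesis at the end of the Introduction allows survival to differ between the treatments, so the loss may differ by arm.

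If both hold, the arm with more deaths keeps the smaller ventricles and looks better on the primary endpoint even when neither treatment affects remodeling. The propensity weights balance the arms as they stood at treatment and do not undo selection that happens later. The primary result could then point the opposite way to all-cause mortality, the main secondary endpoint, in a study meant to inform guidelines.

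**Working it through.** **Inputs from section 3:** 384 surgical and 246 transcatheter patients (384 + 246 = 630), 80% power, two-sided alpha 0.05. **From section 4.1:** 50% mortality, horizon not given. **Assumed, not in the article:** survival by arm, the correlation between LVEDVI and death liability, and the reoperation hazard.

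**1. The plan's own sample size.** The calculation cannot be reproduced, because the article gives no effect size, SD, rates or allowance for death. Back-solving for a difference in means:

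(1.960 + 0.842) × √(1/384 + 1/246) = 0.229 SD.

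Read as a difference in proportions, 630 patients detect about 10 to 11 percentage points.

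**2. Power when only survivors contribute.** With 50% dead in each arm, 192 + 123 = 315 remain. The standard error is √(1/192 + 1/123) = 0.1155, and 0.229/0.1155 = 1.98, so power is Φ(1.98 − 1.96) ≈ 51%. The proportion scale also gives about 51%. Other assumed survival, surgical/transcatheter: 70/70 gives 65%, 60/40 gives 48%, 40/40 gives 43%.

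**3. Bias from survivor selection, no true effect.** Let LVEDVI be standard normal in both arms, with correlation ρ to a normal death liability. With survival proportion s and z_s its normal quantile:

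E[LVEDVI | survive] = −ρ·φ(z_s)/s.

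| Survival in the two arms | φ(z_s)/s | Difference | ρ = 0.3 | ρ = 0.5 |
|---|---|---|---|---|
| 50 / 50 | equal | 0 | 0 | 0 |
| 55 / 45 | 0.720, 0.880 | 0.160 | 0.048 SD | 0.080 SD |
| 60 / 40 | 0.644, 0.966 | 0.322 | 0.097 SD | 0.161 SD |

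In each unequal row the arm with more deaths has the lower mean LVEDVI among survivors. As a cross-check, a logistic death model with mortality 40% against 60% gives 0.08, 0.13 and 0.18 SD for death odds ratios of 1.5, 2 and 3 per SD of LVEDVI.

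**4. Bias against what survivors can detect.** The detectable effect must refer to the same survivors:
- 60% surgical and 40% transcatheter survival: 2.802 × √(1/230.4 + 1/98.4) = 0.337 SD.
- The reverse: 2.802 × √(1/153.6 + 1/147.6) = 0.323 SD.

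The ratio runs from 0.097/0.337 = 29% to 0.161/0.323 = 50%.

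**5. Reoperation.** Assume constant independent hazards and 50% mortality at 10 years, so the death hazard is ln 2/10 = 0.0693 per year. With reoperation hazard h, one minus Kaplan–Meier is 1 − exp(−10h), and the cumulative incidence is h/(h + 0.0693) × [1 − exp(−10(h + 0.0693))].
- h = 0.02: 18.1% against 13.2%, a ratio of 1.37.
- h = 0.01: 9.5% against 6.9%, a ratio of 1.38.

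For a Kaplan–Meier figure of 20%, the overstatement runs from 18% at 30% mortality to 68% at 70% mortality.

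**The case against.** **The rule does not by itself require a complete-case analysis.** Declining to supplement data rules out imputation. A likelihood-based model of the repeated echocardiograms would be compatible with it, and not imputing a volume for a dead patient is defensible because no such volume exists. This stands in part: the deeper gap is the unstated handling of death, and imputation alone would not fill it. But section 3 names no model that would use the repeated measurements, so the text as written leads to the survivors' comparison.

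**The 50% is soft.** A reader might infer that the plan expects half of each arm to die within 10 years. The article does not say so: the figure has no horizon and is attached to the surgical techniques, with transcatheter mortality mentioned separately and without a number. Every result using 50% is therefore conditional.

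**A survival gap is not established.** The hypothesis says only that outcomes may differ. The surgery-versus-transcatheter comparisons in section 4.2 found no significant survival difference (hazard ratio 0.86, p = 0.541, to three years; p = 0.909 at two years). Those horizons are shorter than ten years, but they are the article's evidence, and equal survival gives no bias in the model used here.

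**Mortality is visible elsewhere.** It is the main secondary endpoint, death is part of the composite of major adverse cardiac events, and days alive and out of hospital are analysed. A reader could notice a conflict with LVEDVI, but none of these corrects the primary comparison.

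**Reoperation.** A reader might infer that only Kaplan–Meier and Cox will be used and that reoperation risk will be overstated. The test list is open-ended and the estimator for reoperation is not named. A Cox model censoring deaths gives a valid cause-specific hazard ratio. Only absolute risks read from Kaplan–Meier would be affected.

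**Conclusion.** The point holds for the primary endpoint. It concerns a rule the article states, not detail left to an analysis plan: applied to a 10-year echocardiographic measure in a high-mortality population, that rule yields a comparison of imaged survivors, and baseline weighting does not repair it.

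The loss of power needs no survival gap: about 51% instead of 80% if half of each arm has died, and about 65% if 30% has. The bias does need one: about 0.05 to 0.16 SD toward the arm with more deaths for survival between 55/45 and 60/40, and none if survival is equal. It is tempting to divide 0.10 to 0.16 SD by the 0.229 SD detectable with all 630 patients and report 42 to 70%. That mixes two populations; the like-for-like figure at 60/40 is about 29 to 50%.

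The survival gap, the correlation and the 10-year reading of the 50% are assumptions. The documents do not show that the bias will occur, nor that it would favour a particular treatment. The reoperation point is smaller and applies only where absolute risks are reported.

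**What to change.** 1. Limit the sentence on incomplete data in section 3 so that it does not govern the primary endpoint or the propensity-score covariates.
2. State the estimand for LVEDVI when a patient dies before 10 years.
3. Add a propensity-weighted analysis that ranks death before 10 years below any observed LVEDVI. It targets a composite of death and remodeling, so it should be reported as such and not as a check on another model.
4. For echocardiograms missing in living patients, use all scheduled echocardiograms in a weighted longitudinal model. A joint model with death can be a sensitivity analysis if its target is stated, since its 10-year contrast extrapolates LVEDVI past death.
5. Multiply impute missing baseline covariates used in the propensity score.
6. Where absolute risks of reoperation or mitral re-intervention are reported, use cumulative incidence with death as a competing event. Cox models censoring deaths can stay, labelled as cause-specific.

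The cost is revised wording, extra programming and some modelling assumptions to defend. The echocardiographic and mortality data are already planned, so no new data are needed.

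### No regression named in Section 3 fits the continuous primary endpoint (LVEDVI), so the doubly robust estimator lacks a stated outcome model and baseline LVEDVI is not named as a covariate

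*Protocol article*

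**What the plan says.** **Endpoint.** Section 2.2.1 defines the primary as "the degree of LV remodeling as assessed by the Left Ventricular End-Diastolic Volume Index (LVEDVI) at the 10-year follow-up". Section 2.3, under endpoint definitions, describes it as "quantifying the change in the Left Ventricular End-Diastolic Volume Index (LVESVI) at the time of hospitalization and at regular intervals" after the procedure. There the name spells end-diastolic and the abbreviation is the end-systolic one. Neither place gives a responder cut-off.

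**Models.** Section 3 says "Multivariable analyses will be conducted employing the logistic regression model and the Cox proportional hazards model", and repeats the statement later in the same paragraph. Variable selection belongs to one of the two models: "The variables to be included in the logistic regression analysis will be selected using the Lasso-based variable selection method".

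**Tests.** The tests that could take a continuous outcome (Student's t, Mann–Whitney, Kruskal–Wallis, Wilcoxon) appear under this sentence: "A range of statistical tests will be employed in the univariate analysis".

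**Confounding.** For the effect of exposure on outcomes in general, "a doubly robust approach will be employed comprising combination regression with inverse probability treatment weighting (IPTW) by propensity score". The type of regression is not given. On covariates, the text says only that "a propensity score that balances for covariates will be developed with the objective of minimizing discrepancies between the groups in question".

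**Sample size.** Section 3 gives 630 patients (384 surgical, 246 transcatheter), 80% power and two-sided alpha 0.05, for a difference in the rate of reverse remodelling. It states no rates, difference or SD.

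**The concern.** Logistic regression needs a binary outcome and Cox regression a time-to-event outcome. LVEDVI, as a 10-year value or as a change, is neither. Section 3 is not silent about models. It lists them, and the list has none that can serve as the outcome half of a doubly robust estimator for the primary endpoint. Double robustness means protection if either the propensity model or the outcome model is correct. Without an outcome model that fits, the primary has only the weighting half.

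Baseline LVEDVI matters because treatment was not randomised. Sections 2.1.2 and Table 4 leave the choice of procedure to each center's team, so the groups may well start with different ventricular volumes. Weighting deals with that only if baseline LVEDVI is in the propensity score, and Section 3 does not say that it is.

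The three forms of the endpoint (10-year value, change, rate) also answer different questions. Of these, the named models fit only the rate, which is the one left undefined.

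**Working it through.** **1. The plan's own figure.** The 630 cannot be reproduced, because no effect size, SD or rates are given. It can be solved backwards.

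- Inputs from Section 3: n1 = 384, n2 = 246, power 0.80, two-sided alpha 0.05.
- Continuous outcome: detectable difference = (1.960 + 0.842) × √(1/384 + 1/246) = 2.802 × 0.0817 = **0.229 SD**.
- Binary outcome, pooled two-proportion formula: 20% against 29.8% (9.8 points), or 40% against 51.4% (11.4 points).

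So 630 is compatible with a continuous or a binary primary and does not settle which was meant. Section 4.1 mentions 50% mortality. If, as an assumption, only half of each group had a 10-year echo, the figures become 0.324 SD and about 14 to 16 points.

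**2. Does the form of the endpoint matter?** Let D0 be the between-group difference at baseline and D10 the difference at 10 years. The difference in change is D10 − D0. The two forms therefore differ by exactly D0, whatever the correlation.

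**3. Size of the shift if imbalance remains.** Assumptions, none from the document: equal SD at both times, residual D0 = 0.3 SD, baseline-to-follow-up correlation r = 0.5 to 0.7. Relative to the baseline-adjusted effect:

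| Form | Shift | r = 0.5 | r = 0.7 |
|---|---|---|---|
| 10-year value | r × D0 | +0.15 SD | +0.21 SD |
| Change score | (r − 1) × D0 | −0.15 SD | −0.09 SD |

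The signs are opposite. Against 0.229 SD, the shifts range from 39% (0.09/0.229) to 92% (0.21/0.229) of the detectable effect. Weighting that balances baseline LVEDVI would bring D0, and so both shifts, towards zero.

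**4. Precision.** Relative variance is 1 for the 10-year value alone, 2(1 − r) for the change score and 1 − r² with baseline as a covariate. Power at a true difference of 0.229 SD with all 630 patients, ignoring any loss from weighting:

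| Analysis | r = 0.3 | r = 0.5 | r = 0.7 |
|---|---|---|---|
| 10-year value only | 0.80 | 0.80 | 0.80 |
| Change score | 0.66 | 0.80 | 0.95 |
| Baseline as covariate | 0.84 | 0.90 | 0.98 |

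For comparison, splitting a normal outcome at the median keeps 2/π = 64% of the information and gives power of about 0.61. The document does not propose such a split; the figure only shows what fitting LVEDVI to a logistic model could cost.

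**The case against.** **What a reader might infer, and why it goes too far.**

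- *The primary must be either unadjusted or dichotomised.* This does not follow. Section 3 commits to weighting and to a doubly robust estimator for outcomes generally. A propensity-weighted mean difference in LVEDVI is adjusted and needs no cut-off.
- *Baseline LVEDVI is never used.* Section 2.3 describes a change that starts from the hospitalization measurement, so baseline enters through the change score. It may also be among the propensity covariates, which are not listed.
- *The comparison is biased by 0.15 to 0.21 SD towards the group with smaller ventricles.* That holds only for an unweighted comparison of 10-year values with an assumed 0.3 SD imbalance. With a change score the sign reverses.

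**Further points for the plan.** The logistic model may be meant for the propensity score: Section 1 links LASSO to the propensity-matched cohorts. Outcome models by endpoint and covariate lists are also commonly left to an analysis plan, and this is a condensed article.

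**What stands.** These arguments remove the claim of demonstrated bias. They do not supply a model. If logistic regression is the propensity model, Cox is the only outcome regression left, and it does not fit LVEDVI either. The article chose to list its multivariable models and gave a list that does not match its primary endpoint. A change score does use baseline, but at the assumed correlations it is less precise than covariate adjustment (0.80 against 0.90 at r = 0.5; 0.95 against 0.98 at r = 0.7).

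**Conclusion.** The point holds as a mismatch between the primary endpoint and the models named for it. No named regression fits continuous LVEDVI, the outcome half of the doubly robust estimator is unspecified for the primary, baseline LVEDVI is not named as a covariate in either half, and the sample size is set on an undefined rate. This can be read directly from Sections 2.2.1, 2.3 and 3 and needs no assumption.

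The consequences do rest on assumptions. That the two continuous forms differ by the baseline difference is algebra. The shifts of +0.15 to +0.21 SD and −0.15 to −0.09 SD, and the power figures, depend on an assumed imbalance and assumed correlations. They show that the unmade choice could matter relative to 0.229 SD, not that the result will be biased.

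**What to change.** In Section 2, state one form of the primary: LVEDVI at 10 years, continuous, with the abbreviation in Section 2.3 corrected to match. In Section 3, add text to this effect:

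> The primary endpoint is analysed by an inverse-probability-weighted linear model for LVEDVI at 10 years, with treatment and baseline LVEDVI as covariates and robust standard errors. Baseline LVEDVI is also included in the propensity score. The result is the adjusted mean difference in mL/m² with its 95% confidence interval.

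A weighted mixed model over the post-procedure echoes is an alternative. The echo times would then have to be listed, since the article speaks only of regular intervals.

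Keep logistic regression for the propensity score and binary outcomes, and Cox regression for time-to-event outcomes. Restate the sample-size basis on the LVEDVI scale with its difference and SD, or define the rate and its cut-off if a responder endpoint is really intended.

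State how deaths before 10 years are handled and square this with the rule that incomplete data are not supplemented. With the 50% mortality mentioned in Section 4.1, a mixed model would implicitly extrapolate LVEDVI beyond death, and a model on observed 10-year values describes survivors only.

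**Cost.** A paragraph or two and standard R code, using the hospitalization and follow-up echoes already planned. The small downside is that the handling of death must be settled explicitly.
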